### Control competence for physical training

A self-report measurement [13] is used to assess control competence for physical training. This measure consists of six items with responses ranging from strongly disagree (1) to strongly agree (5).

### Cognitive domain

To assess the health-related fitness knowledge, a questionnaire including a performance test is administered to the students. This questionnaire contains 27 complex multiple choice, matching, and short answer items that we developed and validated in-house.

### Physical domain

The physical domain is assessed by examining physical fitness, which includes three strengthening exercises (standing long jump, push-ups, and sit-ups) that are part of a standardized physical fitness test (Deutscher Motorik Test, German motor test) [36] and an endurance test (shuttle run) [37]. During the shuttle run, the maximum heart rate is measured with a heart rate monitoring system (acentas Herzfrequenz Monitoring™ [38]). Furthermore, we measure perceived physical fitness using the physical fitness subscale (four items: well-trained, vigorous, fit, and strong) of the self-assessment scale for perceived physical state (PEPS) [39]. Students provide their responses on a 6-point Likert scale with a range from 0 (not at all) to 5 (strongly).

### Motivational domain

In order to determine the motivational domain, participants provide information regarding their interest in training, physical fitness and health as well as their affective and cognitive attitudes towards the health effects of PA. To operationalize interest, we have developed four items based upon PISA 2006 [40]. Accordingly, we use a questionnaire (four and three items) to assess their attitudes; previous studies have used this questionnaire in adolescents (e.g., Demetriou) [8]. For all scales, students choose from five possible responses on a Likert scale ranging from 1 (strongly disagree) to 5 (strongly agree).

#### Student characteristics

Students report their gender and month of birth on a questionnaire. Standing height and weight are assessed with a regular scale and a portable weight scale and are used to calculate body mass index (BMI). The BMI is then converted into BMI percentiles based on German reference data [41]. Standing height and weight are also necessary to evaluate accelerometer data obtained when measuring activity during PE classes.

Moreover, we capture self-reported PA behavior using the Physical Activity, Exercise, and Sport Questionnaire (BSA- F: derived from German: Bewegungs- und Sportaktivität Fragebogen) [42]. The BSA-F recalls exercise and sport activities that are usually undertaken and asks for type of PA, frequency per week, and duration of each individual PA. We slightly modified the main question from the original scale in order to gain more differentiated insight in the PA behavior of adolescents with regard to PA in sports clubs and during leisure time.

To operationalize motivational factors and further aspects of PAHCO, we use a five-point Likert scale ranging from 1 (strongly disagree) to 5 (strongly agree), to assess the following:Interest in ball games (3 items), interest in strength training (3 items), and interest in endurance activities (3 items) developed following PISA, 2006 [40].Motives for being physically active (10 items) [36].Control competence for PA-related affect regulation (4 items) [13].PA-specific self-regulation competence (3 items) [13].

#### Class characteristics

As a potential control variable, we also ask students to evaluate their teachers’ instructional quality on a five-point Likert scale (ranging from strongly disagree to strongly agree) following general and PE-specific validated questionnaires [43–45]:Classroom management: monitoring (2 items); discipline (2 items); goal orientation (2 items).Student orientation: supportive climate (2 items); motivation (2 items).

During PE classes, we provide an objective measurement of the duration and intensity of PA once in each class (IG and CG) using validated accelerometer sensors (Move III sensor, movisens GmbH, Karlsruhe Germany), which have also been used in previous studies [46–48]. The sensors triacially measure PA; students wear these sensors attached to their right hips with a clip during class.

#### Teacher characteristics

In order to measure teachers’ attitudes towards core components of the intervention (contents and methods), we administer a questionnaire to all teachers. In the questionnaire, we assess attitudes towards cognitive and reflective contents in grade level 9 in PE (adaption following Rischke, 2009 [49]; 6 items) and attitudes towards health and physical fitness contents in grade level 9 (an adaption of the student-scale, health and physical fitness as a subject of discussion, developed following Hoffmann [50] and further extension considering the curricula contents of Baden-Wuerttemberg, Germany; 7 items). For the first scale, we provide six possible responses on a Likert scale ranging from 1 (not important) to 6 (very important). For the second scale, participants choose from five possible responses on a Likert scale ranging from 1 (strongly disagree) to 5 (strongly agree). In addition, a semi-structured interview is conducted with intervention group teachers in which their attitudes regarding the intervention are further explored after the intervention.

#### Assurance and assessment of fidelity components

To assure that the core components of the intervention are implemented as planned [6, 7], we developed a (implementation) fidelity protocol parallel to the treatment manual following Toomey and colleagues [30] (Fig. 2). The fidelity protocol entails techniques, methods, and process measures to provide, ensure, and record fidelity information on intervention design, teacher training, intervention delivery, and intervention receipt during the main study [7, 29, 30]. We developed and optimized these methods and techniques in our two pilot studies (Fig. 2) and partially followed the experience gained in a former intervention study in a school context [8]. Furthermore, the pilot studies supported the identification of confounding factors and factors to improve the quality of intervention delivery by increasing teachers’ acceptance of and positive attitudes towards the interventions.

### Intervention design

The fidelity component, intervention design, ensures that the study can be replicated and evaluated in relation to its underlying theory [7, 29]. Thus, we precisely describe both treatments in the treatment manual along with the theoretical model of PAHCO and the theoretical basis of the tasks. The treatment manual includes an exact description of the interventions, equipment, and materials needed for the intervention and the self-report forms for the intervention group. Furthermore, control group teachers also receive a standardized process description (including self-report forms) for their lessons. Since the treatment and control conditions take place during regular PE lessons, we assume that the dose is the same within conditions and also equivalent across conditions.

### Teacher training

During the main study, the intervention group teachers participate in a standardized training right before the start of the intervention. The training takes place at the teachers’ schools to reduce expense and increase their compliance. During the two-hour training session, teachers receive information about intervention theory, the goals of the study, and the contents of the intervention, including its special features and troubleshooting. All intervention group teachers undertake the same training with the same two main researchers, but their individual experiences and attitudes also factor into the process; every training session is limited to one to three teachers in order to ensure best possible learning outcomes. During the training, the researchers focus especially on the structure of PE lessons in the run/game play intervention and also regularly provide support in the treatment manual trying to avoid drift over time as the process is new to many of the teachers.

### Intervention delivery

Monitoring of the intervention delivery is considered as the heart of fidelity [7]. To ensure adherence to the treatment manual at the class level, we use the following process measures: First, two observers conduct one announced observation per class that focuses on the intervention delivery and assesses performance using standardized surveillance sheets. Second, the teachers send posters with the results of each lesson (students’ assumptions and defined outcomes of each lesson: Steps 2, 4, and 5 of the learning tasks) in the form of a photo protocol. Third, after the intervention, student booklets provide insight into the students’ completion of intended worksheets during class. Fourth, intervention group teachers fill out the self-report form which assesses intervention delivery of the different steps of the learning process, any deviations, and potential incidents. Control group teachers also complete a self-report form to record their class contents. This process indicates whether both intervention and control group teachers do what is expected and helps to identify differences between those groups. After the completion of the intervention, we conduct also a semi-structured interview that focuses on intervention delivery and optimization of implementation. In cases where disruptions occur during the intervention delivery, the teachers’ instructional quality is rated during the observation by the observers (classroom management, student orientation, positive learning environment [43–45]).

### Intervention receipt

Further, we document the intervention receipt to assess whether participants receive the treatment, to determine whether the participants comprehend and use the treatment during the session, and to identify the extent to which participants are engaged in the content of the treatment [7].

We also assess students’ perception with regard to core components of the intervention as follows [43, 50, 51]:Health and physical fitness as a subject of discussion in PE (contents, 6 items) [50].Perception of cognitive and reflective contents (methods): Cognitive activation (3 items) [43]; methodical reflection (3 items) [51].

We determine student responsiveness by their self-determined learning motivation and also their acceptance and evaluation of the intervention as follows [8, 52]:Self-determined learning motivation: self-determined interest (3 items) and self-determined identified learning motivation (3 items) [52].Acceptance and evaluation of the intervention: Evaluation of health and physical fitness-related intervention programs; items following the evaluation of HealthyPEP [8], tested and optimized in Pilot Study 2 2017; (8 items and 2 short answer questions).

Participants are asked to provide their responses using a five-point Likert scale ranging from 1 (strongly disagree) to 5 (strongly agree). In addition, to examine whether students receive the intervention as intended, the teachers maintain an attendance list.

### Data collection and management

Trained researchers are expected to follow standard operating procedures to collect and enter data. The operational research team consists of two main researchers, a small group of researchers who support organization and process measures, and a group of research assistants who conduct any other necessary assessments and data entry. Within the test manual all standard operating procedures are documented in great detail and prepared documentation forms are used to describe all incidents and deviations from the test manual during data collection. Additionally, teachers regularly send their photo protocol of the posters digitally after each class to the main researchers. Teachers provide the attendance lists as well as the self-report forms and the students’ booklets after the intervention. These booklets are then scanned and sent back to the teachers so that students can keep their booklet and results acquired during the PE lessons. The same two main researchers conduct and record the interviews with the intervention group teachers. We use F4transkribt to transcribe the interviews. We transfer the quantitative data into a secured electronic database (IBM SPSS Statistics) and double- check the information. We also monitor existing data of all measurements anonymously for students and teachers in separate files. The research assistants (*n* = 27) who conduct data collection at three time points and perform the data entry are not informed about the respective group allocation. However, we cannot guarantee blinding throughout the entire study due to data processing and communication between test coordinators and teachers during the assessments.

### Data analysis

Statistical analysis will be conducted, analyzed, and reported according to the CONSORT statement for cluster RCTs [53, 54]. The overall analytic structure uses a structural equation modeling framework with student level variables and class level variables considering the special feature of nested data (e.g. Mplus: TYPE = COMPLEX). We will use a descriptive analysis to establish recruitment and dropout rates and the distribution of baseline characteristics and all outcomes post-intervention and at the 8–12 week follow-up.

The main analysis involves two a priori comparisons; both intervention groups (run/game play) will be compared to their control groups (run/game play). The analysis will estimate differences at the post-test and during follow-up between the two trial arms (IG-run vs. CG-run /IG-game play vs. CG-game play) after adjusting for baseline data. We will examine these differences using linear regression models with control competence for physical training and domains (cognitive, physical, motivational) as outcomes, the respective pretests as a covariate, and an IG-dummy as a predictor.

For the purpose of a sensitivity analysis, we will compare outcomes either based on the intention-to-treat (ITT) principle with classes (clusters) and students analyzed according to the study groups, or on complier average causal effects [55], which has already been used in prior studies [56]. We also will compare the differences between intervention groups. A multiple group analysis will enable us to estimate the average effects for the run/game play intervention and will allow us to test differences between the run and game play groups.

Further, we will conduct a moderation analysis (multiple group model) that accounts for gender and interest in strength and endurance activities, and respectively, in ball games.

We will carry out a mediation analysis to evaluate the effect of the intervention on physical fitness (strength and endurance) as well as on perceived physical fitness and to what extent this influences the efficacy of the interventions on the cognitive and motivational domain as well as on control competence for physical training.

As a customary practice in longitudinal analysis, it is assumed that there are co-correlated residuals over time. Therefore, model comparisons of models with correlated residuals versus models without such correlations are planned.

In general, we expect unsystematic missing data due to absence of students (illness, etc.) on test days. We will analyze systematic occurring missing data with a lost-to follow-up analysis (students) and with the teacher interview. Any “missing at random” data will be replaced using multiple imputation methods. We will report the amount of missing data as a percentage of the main outcomes along with the data recovered in the imputation analysis.

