### Sample size

We determined power calculations prior to the main study to determine the optimal sample size using a mixed-procedure in SAS (multi-level model, restricted ML-estimator). The required number of participants was calculated based on the estimated effect upon control competence for physical training and health-related fitness knowledge by considering available data from previous studies. We determined that a difference of d = 0.30 between the intervention (IG-run, IG-game play) and control groups (CG-run, CG-game play) should be identified with ≥80% power and a 0.05 one-sided significance level. If we assume that an average PE class contains 26 students, the study would require at least 10 PE classes in each group (IG-run, IG-game play, CG-run, CG-game play) according to the power analysis. Therefore, we added four additional classes per intervention group to avoid a reduction in statistical power if a class would withdraw from the study.

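### The clustering method named for the analysis is mildly liberal with 24 classes per comparison, and more so for gender contrasts; a small-sample correction would cure this cheaply

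*Protocol article*

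**What the plan says.** The Data analysis section sets a structural equation modelling (SEM) framework for all analyses and deals with classes by "considering the special feature of nested data (e.g. Mplus: TYPE = COMPLEX"). Within it, "The main analysis involves two a priori comparisons; both intervention groups (run/game play) will be compared to their control groups (run/game play"). Each comparison is a linear regression with "the respective pretests as a covariate, and an IG-dummy as a predictor". On gender, "we will conduct a moderation analysis (multiple group model) that accounts for gender" and interest in the activities. The article names no degrees of freedom, t reference or small-sample variance correction.

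The Sample size section used a different kind of model, "using a mixed-procedure in SAS (multi-level model, restricted ML-estimator"). It required that d = 0.30 "should be identified with ≥80% power and a 0.05 one-sided significance level". "If we assume that an average PE class contains 26 students", then "the study would require at least 10 PE classes in each group".

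Table 1 gives the classes actually allocated: 14 vs 10 for run and 13 vs 11 for game play.

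**The concern.** The sandwich standard error is justified as the number of clusters grows. With few clusters it has two faults that act in the same direction. Residuals are smaller than the true errors, so the variance is underestimated. The normal critical value also ignores that the variance was estimated from few independent units. Both favour declaring an effect, in a trial designed to show superiority over regular lessons. The same inference would be applied to several outcomes, two programs and two time points, and to the gender hypothesis that helped motivate the game-play arm. At stake are somewhat too many false positives and intervals that are somewhat too narrow. The point estimates are not affected.

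**Working it through.** **1. Classes and students (Table 1).**
- Run: 7 + 7 = 14 vs 5 + 5 = 10 classes; 112 + 143 = 255 vs 74 + 76 = 150 students.
- Game play: 6 + 7 = 13 vs 6 + 5 = 11 classes; 106 + 130 = 236 vs 119 + 100 = 219 students.
- Each comparison has 24 classes. Within one gender there are 12 each: 7+5 (run, male), 7+5 (run, female), 6+6 (game play, male), 7+5 (game play, female).
- Overall there are 860 students in 48 classes, 17.9 per class.

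The Randomization text gives Wave 3 as 10 male and 11 female classes, and Table 1 gives 11 and 10. I use Table 1; the other split would move one class between genders and leave the gender conclusion unchanged.

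**2. The plan's own figure.** Without clustering, n per group = 2(1.645 + 0.842)²/0.30² = 137.4, so 138. Ten classes of 26 give 260, a design effect of 260/138 = 1.88. Setting 1 + 25·ICC = 1.88 gives ICC ≈ 0.035. If the pretest explains 25% or 50% of the variance, the ICC can reach about 0.06 or 0.11 (normal approximation). Ten classes per group is therefore attainable, but it cannot be reproduced uniquely because no ICC or pretest correlation is stated.

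**3. Rough calculation of the error rate.** Let r be the mean sandwich standard error divided by the true one. For C classes the rejection rate is roughly P(t with C − 2 df > 1.645·r) one-sided and 2·P(t > 1.96·r) two-sided.

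| Classes (df) | r | one-sided | two-sided |
|---|---|---|---|
| 24 (22) | 1.00 | 5.7% | 6.3% |
| 24 (22) | 0.96 | 6.4% | 7.3% |
| 24 (22) | 0.92 | 7.2% | 8.5% |
| 12 (10) | 1.00 | 6.6% | 7.8% |
| 12 (10) | 0.91 | 8.3% | 10.5% |
| 12 (10) | 0.85 | 9.6% | 12.7% |

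The rows with r = 1 show what the normal reference alone costs; the rest comes from the short standard error.

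**4. Simulation under the null.** Posttest was regressed on pretest and a group dummy, with Table 1 class and student totals and the sandwich variance (X′X)⁻¹(Σ X_g′e_g e_g′X_g)(X′X)⁻¹, where g indexes classes. Critical values were 1.645 and 1.96. Assumptions not in the article are ICC 0.02 to 0.20, a pre-post correlation of 0.6 and the spread of class sizes. The results below use 8,000 runs per setting and unequal class sizes. The second figure in each cell applies a factor C/(C − 1) to the variance.

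| | 24 classes | 12 classes (one gender) |
|---|---|---|
| r | 0.92-0.94 / 0.94-0.96 | 0.85-0.88 / 0.89-0.91 |
| one-sided 5% | 6.4-7.2% / 6.0-6.8% | 8.5-9.5% / 7.9-8.6% |
| two-sided 5% | 7.6-8.5% / 7.1-8.0% | 11.0-12.2% / 9.7-10.8% |
| class-level t-test, one-sided | 4.7-5.5% | 4.7-5.5% |

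With near-equal class sizes and the factor, the results are a little milder: two-sided error goes down to about 6.5% for 24 classes and about 9.3% for 12, and the main-comparison standard error is as little as about 2.5% too small. The ICC hardly matters. The class-level t-test holds its level, so the excess comes from the sandwich with the normal reference.

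**5. Gender moderation as planned.** The multiple-group model tests the difference between the effects in boys and girls, using all 24 classes of a comparison. With near-equal class sizes and the factor, two-sided rejection is 7.1-8.9% (4,000 runs per setting for most of these figures, ICC 0.03 to 0.15).

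**6. A crude correction is not enough within gender.** The C/(C − 1) factor with a t reference on C − 2 df brings one-sided error to 5.2-6.0% with 24 classes but only to 6.1-6.8% with 12.

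**The case against.** The strongest reply is that the option is only an example and that degrees of freedom and variance corrections belong in an analysis plan, which is not shown. This stands in part: such a plan could already contain the correction. But the article does name a method, the only one, and that method in its usual form is the one examined here. It is also fair that clustering is taken into account, that no estimate is biased and that the main inflation is one to two percentage points one-sided.

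Three stronger readings are tempting, and the article does not support them.

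- **Gender error of 9-12%.** This belongs to separate tests in boys and in girls. The article plans a moderation model, whose difference test uses 24 classes and rejects about 7-9%. Pooling the two programs would also give 24 classes per gender.
- **More parameters than classes.** A latent pre/post model for the six-item scale could have more free parameters than 24 classes, which would leave the sandwich rank-deficient. The article describes the main comparisons as linear regressions and does not specify such a model.
- **Power invalidated by the change of model.** Planning with a multilevel model and analysing with cluster-robust errors targets the same contrast and is not a contradiction. The difference lies in the standard error and the reference distribution.

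**Conclusion.** The concern holds in moderate form. If the named method is used uncorrected, main-comparison standard errors are about 2-8% too small. A nominal 5% test then runs at about 6-7% one-sided and 6.5-8.5% two-sided. The gender difference test runs at about 7-9% two-sided, and separately tested gender-specific effects would run at about 9-12%.

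These figures rest on Table 1 counts, a normal reference, an assumed pre-post correlation of 0.6 and ICCs of 0.02 to 0.20. The direction and rough size do not depend on the ICC within that range. For the main comparisons this is a cheap improvement, not a must-fix. It matters more for gender, above all if effects in boys and girls are reported with their own tests.

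**What to change.** State, for the treatment and treatment-by-gender contrasts, one of the following:

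- a linear mixed model with a random class intercept, fitted by REML (the model type used for the power calculation), with Kenward-Roger or Satterthwaite degrees of freedom;
- the planned regression with a CR2 cluster-robust variance and Satterthwaite degrees of freedom;
- a permutation test of class allocation within wave-by-gender strata.

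The SEM can stay for the complier average causal effect, mediation and multiple-group models. If gender-specific effects are reported with their own tests, apply the same correction to them.

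The cost is slightly wider intervals and a little more analysis work. No new data are needed, and the Trial status section shows data collection still running, so the wording can be settled before the final analysis.

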**Fig. 1 Fig1:**
[figure not shown]
The study design containing the planned number of classes and students prior to the study

Over the course of the study, students are tested pre-intervention, post-intervention, and after 8–12 weeks follow-up during their regular school lessons (Fig. 1). The post-intervention and follow-up times may vary for organizational reasons (e.g., school holidays, examinations, canceled lessons). To evaluate the intervention delivery and the students’ duration and intensity of PA, several process variables are assessed during the intervention period. To realize the intervention and comprehensive assessments across 48 classes, the study is carried out in three waves (Wave 1: 1st semester 2017/2018, Wave 2: 2nd semester 2018, Wave 3: 1st semester 2018/2019).

The present study protocol adheres to the Standard Protocol Items: Recommendations for Intervention Trials (SPIRIT) guidelines [31]. The SPIRIT Checklist is provided as supplementary material (see Additional file 1).

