### Randomization

We randomly assigned participants to either the control (CG-run, CG-game play) or the experimental conditions (IG-run, IG-game play). Due to gender-segregated PE classes in Baden-Wuerttemberg, we conducted separate randomization procedures within the gender strata. This investigation had three study periods (Waves 1–3); therefore, we designed the randomization procedure to be performed in three blocks of 16 PE classes. The allocation ratios differed between these three study periods. In Waves 1 and 3, we randomly and equally allocated both male and female PE classes to the four study groups (1:1:1:1). For Wave 2, we used unequal allocation at a ratio of three (IG-run): three (IG-game play): one (CG-run): one (CG-game play). The randomization took place prior to each study period according to the guidelines of Hutchinson and Styles in 2010 [32]. An independent staff member who was not involved in this study used a computer to generate random numbers for each PE class separated by gender and then sorted the cases according to their random numbers. As a result, the allocation to the different study groups remained concealed to the researchers. Table 1 summarizes the allocation ratios as well as the planned number of female and male PE classes separated by study wave.

**Table 1 Tab1:** The planned and effective allocation of the study groups separated by gender and wave

	Allocation ratio and planned number of PE classes		Effective allocated number of participating PE classes after randomization (number of participating students)									
			Male					Female				
Wave	IG-run : IG-game play : CG-run : CG-game play	male/female classes	IG-run (n)	IG-game play (n)	CG-run (n)	CG-game play (n)	Total	IG-run (n)	IG-game play (n)	CG-run (n)	CG-game play (n)	Total
Wave 1	1:1:1:1	8/8	2 (24)	2 (30)	2 (24)	2 (33)	8	2 (45)	2 (34)	2 (25)	2 (31)	8
Wave 2	3:3:1:1	8/8	2 (33)	2 (41)	0 (0)	1 (23)	5^a^	3^b,c^ (56)	2^b^ (39)	0^b^ (0)	1 (24)	6
Wave 3	1:1:1:1	8/8	3 (55)	2 (35)	3 (50)	3 (63)	11^d^	2 (42)	3 (57)	3 (51)	2 (45)	10^d^
Sum		48	7 (112)	6 (106)	5 (74)	6 (119)	24	7 (143)	7 (130)	5 (76)	5 (100)	24

^a^As the recruitment rate had been lower than expected, randomization was conducted with five classes and three additional dummy classes to compensate for the absent three male PE classes

^b^After randomization three female classes allocated to IG-run, IG-game play and CG-run canceled their participation. Therefore, they are not considered in the labeled columns

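### The main model leaves out wave, although allocation ratios differed by wave and Wave 2 has no CG-run class, so the run contrast is partly confounded with wave

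*Protocol article*

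**What the plan says.** The Randomization section of the protocol article describes a design blocked by wave and stratified by gender. On waves: "we designed the randomization procedure to be performed in three blocks of 16 PE classes", and "The allocation ratios differed between these three study periods". On gender: "we conducted separate randomization procedures within the gender strata". The ratio IG-run : IG-game play : CG-run : CG-game play was 1:1:1:1 in Waves 1 and 3 and 3:3:1:1 in Wave 2. The Design section dates the waves; Waves 1 and 3 fall in first semesters and Wave 2 in a second semester.

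The Data analysis section names two a priori comparisons, each intervention group against its own control group, adjusted for baseline. It then spells out the regression: each outcome with "the respective pretests as a covariate, and an IG-dummy as a predictor". Neither wave nor semester appears anywhere in that section. Gender appears only later, in a separate model: "we will conduct a moderation analysis (multiple group model) that accounts for gender and interest in strength and endurance activities".

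**The concern.** Where the allocation probability changes from one randomisation block to the next, the arms are comparable by design only within a block. Pooling the blocks without a block term mixes the treatment effect with any difference between blocks. That imbalance was built into the planned ratios, and recruitment in Wave 2 made it larger for the run comparison, which has no Wave 2 control class at all.

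The pretest covariate removes differences in starting level. It does not remove differences in change between pretest and post-test or follow-up, and those could plausibly differ between a first and a second semester. The Design section itself says that test dates shift with holidays, examinations and canceled lessons. The clustering option that the plan mentions (TYPE = COMPLEX) corrects standard errors, not imbalance between waves. At stake is one of the trial's two main comparisons.

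**Working it through.** **Inputs.** Class and student counts by arm and wave come from Table 1, male and female cells added. The target d = 0.30 and the one-sided 0.05 level come from the Sample size section. The size of a wave effect and the intraclass correlation (ICC) are not in the document and are assumed where used.

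**Planned numbers reproduced.** Each wave was to have 8 male and 8 female classes.
- Each IG: 2 × (2 + 3 + 2) = 14 classes.
- Each CG: 2 × (2 + 1 + 2) = 10 classes.

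Both match the Design section. Even as planned, Wave 2 would hold 6/14 = 43% of each IG and 2/10 = 20% of each CG.

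**Effective numbers.**

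| Arm | Classes W1/W2/W3 | Students W1/W2/W3 | Wave 2 share, classes | Wave 2 share, students |
|---|---|---|---|---|
| IG-run | 4/5/5 = 14 | 69/89/97 = 255 | 35.7% | 34.9% |
| CG-run | 4/0/6 = 10 | 49/0/101 = 150 | 0% | 0% |
| IG-game play | 4/4/5 = 13 | 64/80/92 = 236 | 30.8% | 33.9% |
| CG-game play | 4/2/5 = 11 | 64/47/108 = 219 | 18.2% | 21.5% |

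Table 1 and the text disagree on the male/female split in Wave 3. The counts above add both genders, so they do not depend on it.

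**Bias without a wave term.** Let δ be the Wave 2 shift in outcome, in SD, that remains after pretest adjustment, with Waves 1 and 3 treated as alike. Bias = δ × (Wave 2 share in IG − Wave 2 share in CG).
- Run: 89/255 − 0 = 0.349, so about 0.35 δ.
- Game play: 80/236 − 47/219 = 0.339 − 0.215 = 0.124, so about 0.12 δ.

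| Assumed δ (SD) | Run bias (SD) | Run bias as share of 0.30 | Game play bias (SD) |
|---|---|---|---|
| 0.1 | 0.035 | 12% | 0.012 |
| 0.2 | 0.070 | 23% | 0.025 |
| 0.3 | 0.105 | 35% | 0.037 |

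A shift in favour of Wave 2 flatters the intervention; a shift against it hides part of a real effect.

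**Effect of adding wave, run comparison.** Treat classes as equal units, with the standard error proportional to the factors below.
- Without wave: √(1/14 + 1/10) = 0.414.
- With wave: Wave 1 gives 4×4/8 = 2.000, Wave 2 gives 0 and Wave 3 gives 5×6/11 = 2.727. The sum is 4.727, and 1/√4.727 = 0.460.
- Ratio: 0.460/0.414 = 1.11. The bias from δ is zero, because only within-wave differences are used.
- Power: a nominal 80% one-sided test has a signal of 1.645 + 0.842 = 2.487 standard errors. Then 2.487/1.11 = 2.24 and Φ(2.24 − 1.645) = 72%.

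**Effect of adding wave, game play comparison.** √(1/13 + 1/11) = 0.410 becomes 1/√(16/8 + 8/6 + 25/10) = 0.414, a rise of about 1%.

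**Four-arm model.** Fitting four arm means plus wave to the class layout of Table 1 leaves no bias if the Wave 2 shift is common to running and games. If the shift affects running classes only, the run contrast keeps 0.21 δ, against 0.36 δ (5/14, by class) with no wave term.

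**The case against.** The strongest reply is that the covariate list is not declared closed. The section speaks of student- and class-level variables in general, and the Class characteristics section collects instructional quality as a possible control variable that the quoted sentence also omits. A journal article condenses the plan, and stratification covariates may be set out elsewhere. This stands to the extent that nobody can say from the article that wave will in fact be omitted. It does not rescue the text: the article states the main regression's covariates, and wave is mentioned nowhere in the analysis section.

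Three stronger readings are tempting, and the document does not support them.
- A reader might infer that the run comparison as a whole is confounded with semester. It is not: Waves 1 and 3, both first-semester, hold 9 of 14 IG-run and all 10 CG-run classes.
- A reader might infer that leaving out gender also biases the result. By class, Table 1 shows 7 male and 7 female against 5 and 5 in run, and 6 and 7 against 6 and 5 in game play. Gender is a matter of consistency with the stratification and possibly of precision.
- A reader might infer that false positives are known to be heavily inflated. Under a normal approximation with ICC 0.02 to 0.05 and no gain from the pretest, the one-sided 5% error of the run test would be about 8 to 9% at δ = 0.1, 13 to 15% at 0.2 and 19 to 23% at 0.3, if the shift favours the intervention. All these inputs are assumed, and δ = 0.3 is as large as the whole target effect.

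It is also fair to say that seasonal mechanisms fit the fitness tests better than the self-report scale and knowledge test on which the sample size rests, and that the correction costs power.

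**Conclusion.** The point holds for wave. As written, the main model does not follow the blocks within which classes were randomised, and about 0.35 of any residual Wave 2 shift passes into the run estimate (about 0.12 for game play). The confounding is partial and its direction unknown. The two fractions follow from Table 1 with Waves 1 and 3 taken as alike; the bias in SD units depends on an assumed shift, since the document gives none. Over 0.1 to 0.3 SD the run bias is 0.035 to 0.105 SD, which is 12% to 35% of the effect the trial was sized to detect. The omission of gender is not a source of bias on these counts.

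**What to change.** - Add wave (three levels) as a fixed covariate to every main model.
- State that the Wave 2 IG-run classes have no concurrent control, so that the two-arm run contrast effectively rests on Waves 1 and 3, with 9 versus 10 classes.
- Gender may be added as a stratification factor, for consistency with the design and possible precision.
- A four-arm model on all 48 classes may be reported as well. Its assumption of a common wave effect for running and games must then be stated, because about 0.21 of a running-only shift would remain.

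The text change is a few sentences. The Trial status section says that Wave 3 data collection was still under way, so the change can be made before the analysis. The statistical cost falls on the run contrast: a standard error 10 to 11% larger, which takes a nominal 80% power to about 72%. The 9 IG-run classes that then inform it are below the 10 per group that the Sample size section requires, and this should be acknowledged. For game play the cost is about 1% in standard error.
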